## Abstract

This article reports the study protocol of a nationwide multicentric study in seven Italian regions aimed at assessing the effectiveness of a digitally supported approach for the early screening of frailty risk factors in community-dwelling older adults. SUNFRAIL+ is a prospective observational cohort study aimed at carrying out a multidimensional assessment of community-dwelling older adults through an IT platform, which allows to connect the items of the SUNFRAIL frailty assessment tool with a cascading multidimensional in-depth assessment of the bio–psycho–social domains of frailty. Seven centers in seven Italian regions will administer the SUNFRAIL questionnaire to 100 older adults. According to the answers provided by older adults, they will be subjected to one or more validated in-depth scale tests in order to perform further diagnostic or dimensional evaluations. The study aims to contribute to the implementation and validation of a multiprofessional and multistakeholder service model for the screening of frailty in community-dwelling older adult population.

## 1. Introduction

Demographic changes in Europe and the progressive aging of the population are likely to affect the planning and delivery of health and social services due to the increasing demand for care services and the complexity of the health needs of the over 65 population [1]. Older adults with multimorbidity are a vulnerable subgroup of the population that has been found to have a higher mortality from COVID-19 and a higher risk of adverse outcomes [2]. Furthermore, the COVID-19 pandemic has highlighted the deterioration of the quality of life of older adults due to the drastic change in their social habits and reduced access to health and social services [3].

Frailty in older adults results in reduced physiological reserve, which leads to an increased risk of falls, hospitalization, disability and death [4]. The determinants of frailty syndrome are multiple and interconnected. In addition to the natural physiological changes of aging, multimorbidities, malnutrition, living environment, genetics, social relations and lifestyle also influence the onset of frailty [5]. Frailty limits regular physical and social activity and their related health benefits for older people [6]. The increasing prevalence of frailty has different implications in terms of health needs that require different interventions depending on the time of onset and the socioeconomic background of individuals [7]. Frail people represent an increasing economic burden on healthcare systems [8]. Early screening for frailty risk in community-dwelling older people enables preventive intervention on the clinical and social determinants of frailty and, thus, the prevention of adverse events [9].

The centrality of nursing services in the promotion of health in the older adult population through prevention, education and health information is certainly a topic that has been discussed and added to the agenda of public health systems in recent years [10]. Many Italian regions and all actors involved in the working groups activated by the Programma Mattone Internazionale Salute (ProMIS), the Italian Ministry of Health program for the internationalization of regional health systems [11], have been involved in various ways in the implementation of the family and community nurse (FCN) professional profile. Italian regions are progressively introducing FCN into their health system in a pilot form or through dedicated policies, defining its boundaries, actions and relations [12,13]. The FCN is pivotal for meeting the twin challenges of an aging population and the increasing incidence of long-term conditions in order to prevent adverse events and enable health systems to encourage and ensure the improvement of health and well-being instead of focusing exclusively on the treatment of illness [14].

The European project SUNFRAIL proposes an innovative and integrated approach that takes into account all of the various factors that influence an individual’s state of health towards frailty: environmental, medical, educational, economic and psychological. The SUNFRAIL approach starts from the assumption that frailty is a reversible condition if detected at an early stage and that it must, therefore, be identified first and foremost in primary care and community settings in order to prevent dependency and disability [15].

As a result, the SUNFRAIL project developed a tool for the early identification of frailty in the over 65 population that can be used in different contexts, consisting of only nine items, which can be linked to other in-depth tools for the assessment of specific frailty domains [16]. The SUNFRAIL tool aims to detect frailty risk factors at an early stage, guiding subsequent diagnostic assessments for the identification of health promotion and disease prevention targeted interventions (Figure 1).

The SUNFRAIL tool enables very early screening in primary care, community and specialist services, guiding them to subsequent in-depth clinical and nonclinical investigations with respect to the identified domains of frailty (i.e., physical, cognitive, nutritional and social). It represents a synthesis tool for socio-health integration services, where the physical dimension is not exhaustive but must be associated with the biological, psychological and socio-relational dimensions. Primary care for older adults with multimorbidity is characterized by the fragmentation of care services (general practitioners, geriatricians, territorial specialists, rehabilitators, FCNs, etc.). In this sense, information technology (IT) represents a very powerful tool to support prevention and healthcare activities. In fact, IT has become increasingly widespread and available in recent years, although it is currently only partially validated [17].

Therefore, the ProMIS Working Group on Frailty designed a new service model for the frailty screening of community-dwelling older adults by means of the SUNFRAIL+ platform, an IT tool that supports healthcare professionals by linking the items of the SUNFRAIL tool to additional scales aimed at assessing impaired domains and enabling him/her to develop appropriate intervention strategies. This IT-supported multidimensional approach improves the availability of data on the target population for health professionals to develop targeted interventions in the domains identified as being at risk. In this model, the FCN can act as the first point of contact for individuals and families and play a leading role in disease prevention and health promotion, turning to specialists when more expertise is needed.

## 2. Materials and Methods

### 2.1. Study Design

The SUNFRAIL+ study protocol was developed through a prospective observational cohort study. The study will carry out a multidimensional assessment of older adults, through the SUNFRAIL+ platform, which allows the linking of each item of the SUNFRAIL tool with a cascading multidimensional in-depth assessment of the bio–psycho–social domains of frailty [18]. The study aims to assess the impact of early, integrated and simultaneous “taking care” by health systems on the quality of life of community-dwelling older adults through the SUNFRAIL+ platform. In addition, the study aims to verify the effect of SUNFRAIL+ on the appropriateness of care by the healthcare system and the impact of IT solutions on the organization of services and the workload of professionals.

### 2.3. Participants

Each center will independently recruit 100 ambisexuals, randomly selected older adults. Subjects who meet the following inclusion criteria are eligible to participate: age ≥65 years; living at home; accessing participating centers for social and healthcare services other than those covered by this study; and ability to sign the informed consent. Subjects will be excluded if they are <65 years old; residents in care facilities (hospital and nursing home); have overt frailty or disability; are already enrolled in home care; and are unable to understand the study aims and sign the informed consent.

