### 2.4. Intervention

The study will have a duration of 14 months: 6 months for the first multidimensional assessment (enrolment), 6 months “taking charge” (observation) and 2 months of data analysis and evaluation (follow-up) (Figure 3).

Each center will administer the SUNFRAIL tool to the enrolled older adults and, according to the specific frailty risk factors identified by the answers provided, they will be subjected (at the same time or subsequently) to one or more validated scales (already included in the SUNFRAIL+ platform) in order to perform further diagnostic or dimensional evaluations in the domains identified as being at risk.

In addition, demographic, anamnestic and anthropometric variables will be acquired. The multidimensional assessment through the platform will be carried out by trained personnel.

During the observation phase, older adults will be offered different health promotion activities, depending on the multidimensional assessment. Healthy older adults will be offered collective physical exercise programs and nutritional recommendations. In addition, services will be provided to promote socialization and educational modules dedicated to fall prevention. For subjects with chronic diseases, in addition to health promotion, services for patient empowerment and improved adherence to treatment goals will be provided.

During the follow-up phase, 6 months after enrolment, the SUNFRAIL tool and in-depth tests will be administered again. In addition, during the follow-up, the extent to which the exposure to the interventions has influenced the quality of life of older adults will be measured, and the number of users enrolled by the territorial services based on user care needs will be documented. In addition, the level of satisfaction and usability of the SUNFRAIL+ solution by health and social care professionals will be measured.

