### 2.5. Outcomes

The data from the study will be collected through the following instruments and self-assessment questionnaires:Frailty multidimensional screening: SUNFRAIL tool [16];Prescription adherence: medication adherence report scale (MARS) [19];Nutrition: assessment of adherence to the Mediterranean diet (PREDIMED) [20] and mini-nutritional assessment (MNA) [21];Physical activity: short physical performance battery (SPPB) [22];Fall risk: age-friendly environment assessment tool (AFEAT) [23] and time up and go test [24];Cognitive decline: quick mild cognitive impairment (QMCI) [25] and general practitioner assessment of cognition (GPCOG) [26];Loneliness: geriatric depression scale (GDS) [27];Support network: social provisions scale (SPS) [28];Socioeconomic conditions: self-assessment questionnaire (MUSE) [29];Quality of life: SF-12 health survey [30];Usability: system usability scale [31].

The adherence to medical visits will be measured by means of a questionnaire in which older adults will be asked how many times in the last 3 months they visited the GP, received home nursing visits, went to hospital, went to the emergency room, and had specialist examinations, blood tests or other diagnostic examinations. In addition, older adults will be asked whether they have difficulties in making an appointment with the GP or in getting to the GP’s clinic.

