### 2.6. Statistical Analysis

All complete questionnaires will be analyzed. The statistical analysis will be:(1)Descriptive and exploratory (ADE) with respect to the study population, bringing to light any “features” present in the data;(2)Confirmatory (ADC), focusing on confirming or falsifying the appropriateness of early, integrated and simultaneous care.

For the descriptive analysis, the absolute and relative frequency distributions of all qualitative variables will be calculated, while for the quantitative or semiquantitative variables (e.g., scales from 1 to 10), the main summary and variability indices (mean, median, minimum, maximum, standard deviation, range and interquartile difference) will be calculated.

The main statistical tests will be used for confirmatory analyses, depending on the types of variables: chi-square test, McNemar test for dichotomous data, parametric t-test and Wilcoxon’s nonparametric test for paired data (before–after). All tests will be two-sided, with a 5% significance level. The multiple linear regression model will be used to examine the contribution of the parameters measured during the study (explanatory variables) on the quality of life (score measured by the SF-12 questionnaire, dependent variable).

The analyses will be performed using IBM SPSS Statistics software for Windows, version 26, Armonk, NY, USA, IBM Corp.

With a type 1 error of 5% and a study power of 80%, accepting a 95% confidence level and targeting an improvement of 10% in the SF12 score, the requested sample size will be composed of 195 subjects. The number of 700 clients exceeds the needed number of participants, which can be useful to perform nested analysis.

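### A recruiting contact of a counted type enters the baseline 3-month visit count but cannot enter the 6-month count, so a before-after comparison could show a fall with no effect

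*Protocol article*

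**What the plan says.** All references are to the protocol article.

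- **Entry (2.3 Participants).** Eligible people are those "accessing participating centers for social and healthcare services other than those covered by this study". Each centre recruits 100 people, described as randomly selected. People who "are already enrolled in home care" are excluded.
- **Outcome (2.5 Outcomes).** Adherence to medical visits is measured by questionnaire: "older adults will be asked how many times in the last 3 months they visited the GP". Home nursing, hospital and emergency-room use are counted too, and so is whether they "had specialist examinations, blood tests or other diagnostic examinations".
- **Timing (2.4 Intervention).** "During the follow-up phase, 6 months after enrolment, the SUNFRAIL tool and in-depth tests will be administered again". Nobody has to be attending a service at that point.
- **Analysis (2.6 Statistical Analysis).** The confirmatory tests, chosen by type of variable, include the "parametric t-test and Wilcoxon’s nonparametric test for paired data (before–after" comparison. Tests are two-sided at 5%. The article describes one cohort and no comparison group.

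Nothing in the text removes the recruiting contact from the baseline count.

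**The concern.** Attendance at a service is both the route into the study and something the study counts. A person approached at a specialist appointment or a blood test has at least one counted contact at baseline because that contact is how the centre met them. The second count carries no such condition, and there is no comparison group in which the same artefact would cancel.

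Section 2.1 sets out to verify an effect on the appropriateness of care, and the Discussion lists adherence to medical visits among the services expected to improve outcomes. A built-in fall in contacts could be read as reduced need or as poorer adherence, and it could mask part of a true rise. Centres differ in the services they provide (Strengths and Limitations), so the share affected probably differs by centre and could pass for a difference between centres.

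**Working it through.** The article gives no figure of its own for visit counts. Its sample size of 195 concerns the SF-12 score and does not bear on this point.

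**Inputs from the article:** n=700 (7 centres × 100), two-sided 5% level, 3-month recall, reassessment at 6 months.

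**Assumed inputs, not in the article:**
- *f*, the share recruited at a counted contact: 0.1, 0.25 or 0.5.
- *m*, mean contacts per 3 months in the source population: 2 or 4.
- Person-to-person variation in rates: gamma, shape 1.5.
- *v*, the variance of an independent multiplier on each person's rate in each period: 0 (constant rates) or 0.5.

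**Step 1, timing.** With enrolment at month 0, the baseline recall covers months −3 to 0 and the follow-up recall about months 3 to 6. A contact at month 0 can fall only in the first. With a look-back of L months the second window opens at month 6 − L, so the recruiting contact is missed whenever L is shorter than about 6.

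**Step 2, expected change under no effect.** Baseline = X₁ + I, where I is 1 with probability *f*. Follow-up = X₂, with the same mean as X₁. The expected change is therefore −*f*: −0.10, −0.25 or −0.50 contacts per person. If contact types are analysed separately, each type carries only its own part of *f*.

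**Step 3, variance.** Sampling by attendance over-represents heavy users, so a person's rate λ is gamma with shape 2.5 and scale *m*/1.5.

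- E(λ) = 2.5 × *m*/1.5 = 3.33 (*m*=2) or 6.67 (*m*=4).
- E(λ²) = 2.5 × 3.5 × (*m*/1.5)² = 15.56 or 62.22.
- Var(change) = 2E(λ) + 2*v*E(λ²) + *f*(1−*f*).

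**Step 4, chance of rejection with no true effect.** z = *f* / √(Var/700); rejection = Φ(z − 1.96) + Φ(−z − 1.96).

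Worked case, *f*=0.25 and *m*=2:
- Constant rates: Var = 6.667 + 0.1875 = 6.854, SE = 0.0990, z = 2.53, rejection 71%.
- *v*=0.5: Var = 6.667 + 15.556 + 0.1875 = 22.41, SE = 0.1789, z = 1.40, rejection 29%.

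| *f* | constant, *m*=2 | constant, *m*=4 | *v*=0.5, *m*=2 | *v*=0.5, *m*=4 |
|---|---|---|---|---|
| 0.10 | 17% | 11% | 9% | 6% |
| 0.25 | 71% | 44% | 29% | 12% |
| 0.50 | >99% | 95% | 80% | 33% |

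Simulating the same model with a paired z-test (3,000 replicates per cell) agrees with every cell to within one percentage point. At *f*=0 the test rejects in about 5%, as it should, and at *f* of 0.25 or more practically every rejection is a fall.

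**Step 5, how large *f* must be.** An 80% chance of a false result needs *f* of about (1.96 + 0.84) × SE. For the four columns that is 0.28, 0.39, 0.50 and 0.92.

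**The case against.** **The link from outcome to test is inferred.** Section 2.4 names the SUNFRAIL tool and the in-depth tests as repeated. The visit questionnaire stands apart in section 2.5, and section 2.6 assigns no test to it. This stands, so the point is conditional. Repetition is still the natural reading, given before-after tests and an aim of verifying an effect.

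**There may be no recruiting contact in the window.** Participants are described as randomly selected and the sampling frame is not given. A centre drawing from a list of service users may enrol people whose last contact was long before. Eligibility also covers social services, which the questionnaire does not count. This stands too: *f* may be small, and at *f*=0.1 the inflation is modest.

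**The high rejection rates need constant personal rates.** Correct. Variation between periods lowers them markedly, which is why both sets are shown. A reader might infer that clustering of visits around an illness makes false positives more frequent still. Clustering can enlarge the bias, but it also raises the variance, and the net effect has not been computed.

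**Other forces act on the counts.** Home nursing runs the other way, because people in home care are excluded at entry and that count can hardly fall. Services offered during the observation phase could add real contacts. Both limit the point to particular contact types and to the no-effect case, without removing it.

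**The consequences may be limited.** The article nowhere names a fall in visits as a benefit, the sample size and the regression concern the SF-12, and Strengths and Limitations already concedes that the effectiveness of the prevention services cannot be investigated. This lowers the stakes. It does not justify leaving an avoidable artefact in the visit counts.

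**Conclusion.** The point holds in conditional form. Where recruitment happens at or soon after a counted contact, and the questionnaire is repeated and compared before-after, the no-effect expectation is a change of −*f* contacts per person over 3 months, for the contact types concerned. At n=700 the false-positive rate ranges from close to nominal (6% at *f*=0.1, *m*=4, varying rates) to near certainty (*f*=0.5, constant rates). Those figures rest on an unknown *f* and on assumed means, shape and between-period variance.

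Three stronger readings are not supported:

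- A reader might infer that service use will appear to fall. The article does not fix *f*, so it shows only that this can happen.
- A reader might infer that the artefact arises with any recall window. It needs a look-back shorter than the gap of about 6 months. A 12-month recall at both assessments would include the recruiting contact twice.
- A reader might infer that a true rise of up to one contact per person could be hidden. That needs *f*=1, meaning everyone recruited at a counted contact.

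The correction is still worth making before data collection, because a contact that was not recorded cannot reliably be recovered by a later choice of analysis.

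**What to change.** - **Section 2.5:** word the baseline question so that it leaves out the contact at which the person was recruited, and record that contact's date and type in a separate field.
- **Section 2.6:** make any before-after comparison of visit counts by contact type, on the counts without the recruiting contact. Show the counts with it as a sensitivity analysis, and describe any remaining fall as possibly due to selection on attendance.
- **Do not** impute or subtract a recruiting contact from the centre's type of service alone. The participant may never have reported it, or it may be of a type that is not counted.

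Cost: one reworded question and one extra form field, with no additional participants. The baseline count will be slightly lower, so any true reduction will look a little smaller.

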### 2.4. Intervention

The study will have a duration of 14 months: 6 months for the first multidimensional assessment (enrolment), 6 months “taking charge” (observation) and 2 months of data analysis and evaluation (follow-up) (Figure 3).

Each center will administer the SUNFRAIL tool to the enrolled older adults and, according to the specific frailty risk factors identified by the answers provided, they will be subjected (at the same time or subsequently) to one or more validated scales (already included in the SUNFRAIL+ platform) in order to perform further diagnostic or dimensional evaluations in the domains identified as being at risk.

In addition, demographic, anamnestic and anthropometric variables will be acquired. The multidimensional assessment through the platform will be carried out by trained personnel.

During the observation phase, older adults will be offered different health promotion activities, depending on the multidimensional assessment. Healthy older adults will be offered collective physical exercise programs and nutritional recommendations. In addition, services will be provided to promote socialization and educational modules dedicated to fall prevention. For subjects with chronic diseases, in addition to health promotion, services for patient empowerment and improved adherence to treatment goals will be provided.

During the follow-up phase, 6 months after enrolment, the SUNFRAIL tool and in-depth tests will be administered again. In addition, during the follow-up, the extent to which the exposure to the interventions has influenced the quality of life of older adults will be measured, and the number of users enrolled by the territorial services based on user care needs will be documented. In addition, the level of satisfaction and usability of the SUNFRAIL+ solution by health and social care professionals will be measured.

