### Strengths and Limitations

One of the strengths of the study is the participation of several centers, providing different services but all interacting with the target population along the SUNFRAIL specific domains. This will make it possible to demonstrate that the identification of risk factors for frailty in older adults and their enrolment in prevention and health promotion services should not only take place at a dedicated healthcare facility but in different settings and at different levels of care.

The main limitation of the study is that the intervention strategies of the health systems involved and the services available from health organizations are not uniform. This does not allow the study to be able to investigate the effectiveness of prevention and health promotion interventions to be linked to the screening of frailty risk factors. The exploitation of the study outcomes depends very much on the ability of the centers to link the screening of frailty’s risk factors with the services currently available in the participating centers for prevention and health promotion.

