## 4. Conclusions

The SUNFRAIL+ nationwide multicenter observational study aims to demonstrate the effectiveness of a digitally supported approach for the early screening of frailty risk factors in community-dwelling older adults. The study results will encourage the implementation and validation of a multiprofessional and multistakeholder service model for frailty prevention in community-dwelling older adult populations.

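### The aims claim impact and effectiveness, but a single cohort tested before and after cannot attribute change to the programme, and the Limitations contradict Section 2.4 on the interventions

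*Protocol article*

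**What the plan says.** **Design.** Section 2.1 states that the "SUNFRAIL+ study protocol was developed through a prospective observational cohort study". Section 2.4 adds that "older adults will be offered different health promotion activities, depending on the multidimensional assessment". No unexposed, delayed-start or historical comparison is described in the text available for review.

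**Aims.** Section 2.1: "The study aims to assess the impact of early, integrated and simultaneous" care by health systems on quality of life, delivered through the platform. Section 2.4: "the extent to which the exposure to the interventions has influenced the quality of life of older adults will be measured". Section 4 (Conclusions): the study "aims to demonstrate the effectiveness of a digitally supported approach for the early screening of frailty risk factors"; the Abstract says much the same. The Discussion expects gains in quality of life that come from taking part in the services.

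**Analysis.** Section 2.6 assigns its confirmatory part to deciding whether early, joined-up care is appropriate. The tests listed are chi-square, McNemar, and the "parametric t-test and Wilcoxon’s nonparametric test for paired data (before–after"). A multiple linear regression of SF-12 on the parameters measured in the study is also planned. The sample size is 195 for a 10% improvement in SF-12, with 700 planned.

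**Limitation.** Strengths and Limitations, referring to intervention strategies and services that differ between centres: "This does not allow the study to be able to investigate the effectiveness of prevention and health promotion interventions".

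**The concern.** Section 2.4 says the influence of the interventions on quality of life will be measured. Strengths and Limitations says their effectiveness cannot be investigated. Both statements cannot stand.

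Separately, the impact and effectiveness aims need a contrast between people who did and did not receive the approach, or some other basis for knowing what would have happened without it. A paired test in one cohort supplies neither. It asks whether the mean changed, not why.

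If the plan is followed as written, a significant paired SF-12 result could be reported as confirming effectiveness and used to support the service model that the Conclusions hope to see implemented. A null or negative result could equally hide a real benefit behind an underlying decline.

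**Working it through.** **Step 1. Each aim against what the analysis can deliver.**

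| Aim | Contrast it needs | What is planned |
|---|---|---|
| Impact of care through the platform on quality of life (2.1) | With versus without the platform | Change over time in one cohort |
| Influence of exposure to the interventions (2.4) | More versus less exposed, comparable otherwise | Paired tests without exposure; an SF-12 regression with no exposure term named |
| Effectiveness of the digital screening approach (Abstract, Conclusions) | With versus without the approach | Change over time in one cohort |

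Strengths and Limitations rules out the second row in words. It does not address the third, which fails because there is no comparator.

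**Step 2. Timing.** Section 2.4 gives 6 months of enrolment, 6 of observation and 2 of follow-up, and places reassessment both in the follow-up phase and 6 months after enrolment.

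- Reading A, each person 6 months after their own enrolment: baselines fall in months 1–6 and reassessments in months 7–12. Everyone is reassessed half a year away in season.
- Reading B, the 2-month follow-up phase: reassessments fall in months 13–14. A person enrolled in month 1 or 2 could be seen in the same calendar months a year later. Intervals would run from 12 − 6 = 6 to 14 − 0 = 14 months.

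On both readings every baseline precedes every reassessment and the two periods do not overlap. Secular trend and ageing therefore cannot be separated from an effect. Confounding with season is complete only on Reading A.

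**Step 3. The plan's figure of 195.** Section 2.6 gives alpha 5% two-sided, power 80% and a 10% improvement, but no SD, baseline mean, correlation or test. The figure can be neither reproduced nor refuted. If it came from a paired test, N = ((1.960 + 0.842) × SD of change / delta)², so the standardised change is 2.802/√195 = 0.2006 and the SD of change is 4.98 × delta. For an assumed SF-12 mean of 40 to 50, delta is 4 to 5 points and that SD is about 20 to 25 points. Other assumed set-ups also land close: a two-group total of 198 at mean 40 and SD 10, or a one-sample proportion of 50% against 60% at 194. The illustration below therefore does not use the origin of 195.

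**Step 4. Illustration of drift.** Let the true effect be zero and d be the mean drift in SDs of the change. For a two-sided 5% paired test with N independent complete pairs,

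P(p<0.05) = Φ(d√N − 1.96) + Φ(−d√N − 1.96).

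For d = 0.10:

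- N = 195: d√N = 1.396, so Φ(−0.564) + Φ(−3.356) ≈ 0.287.
- N = 700: d√N = 2.646, so Φ(0.686) + Φ(−4.606) ≈ 0.754.

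| Assumed drift d | 195 pairs | 700 pairs |
|---|---|---|
| 0.05 | 10.7% | 26.3% |
| 0.10 | 28.7% | 75.4% |
| 0.15 | 55.4% | 97.8% |
| 0.20 | 79.8% | >99.9% |

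In points, an assumed 1-point drift with an assumed SD of change of 8 to 12 reaches p<0.05 with probability 0.21 to 0.42 at 195 pairs and 0.60 to 0.91 at 700. The surplus over 195 makes a non-causal shift more likely to be significant. It does nothing to identify the cause.

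**The case against.** The strongest reply is that the study is openly labelled observational, that its authors state a limitation, and that a condensed article need not list regression terms. All of that is fair, and several stronger readings should be set aside.

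- *The exposure question is never analysed.* A reader might infer this from the list of tests. The SF-12 regression takes the measured parameters as explanatory variables, and exposure could be among them. The text supports only that no exposure term is named.
- *The Limitations concede that no effectiveness can be studied.* They concern the prevention and health promotion interventions, and the reason given is non-uniform services, not the missing control. They do not speak to the screening approach.
- *Everyone is reassessed in the opposite season.* True only on Reading A; Section 2.4 can be read either way.
- *Drift would confirm the programme.* The direction is unknown. Section 2.3 excludes overt frailty and disability and states no selection on low SF-12, so ageing would tend to lower scores and could mask a benefit.
- *A drift of 3.7% of the SF-12 score is enough for p<0.05 at 700, and 5.3% is detected with 80% power.* The arithmetic is right: 10% × (1.96/√700)/0.2006 = 3.7% and 10% × √(195/700) = 5.3%. Both require that 195 came from a paired test, which the protocol does not say. A true drift of 3.7% would reach significance only about half the time.

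What remains is the conflict between Section 2.4 and the Limitations, and causal aims without a comparator. An analysis plan could name an exposure term, but it could not create a comparator for the platform in a single cohort or reconcile the two statements.

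**Conclusion.** The point holds and the text is wrong as it stands. Section 2.4 and Strengths and Limitations contradict each other on the interventions. The impact and effectiveness aims in the Abstract, Section 2.1 and the Conclusions cannot be met by paired tests in one cohort. Following the plan would attribute total change to the programme.

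The size and direction of the resulting bias cannot be derived from the protocol. The rejection rates are an illustration that assumes a drift, a zero true effect and independent complete pairs. The conclusion rests on the design and wording, not on those rates or on how 195 was obtained. It also assumes that no comparator is described outside the text available for review; nothing in that text suggests one.

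**What to change.** Reword the Abstract, Sections 2.1, 2.4 and 2.6, the Discussion and the Conclusions so that the study estimates within-person change after SUNFRAIL+ assessment, without causal attribution and in line with Strengths and Limitations. State in Section 2.6 that a significant paired SF-12 test will not be taken as confirming effectiveness. Say in Section 2.4 which reassessment timing applies.

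Optionally, and only if service uptake is recorded for each participant, add a secondary comparison of follow-up SF-12 by uptake, adjusted for baseline SF-12, SUNFRAIL items, centre and calendar month. Report it as an association. Activities are offered according to assessed need, so it stays open to confounding by indication, and it would pool services that the authors say are not uniform. It should not be presumed free: Section 2.4 documents only a number of users enrolled by territorial services, so participant-level recording has to be confirmed first.

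The rewording needs no new data. Its cost is a weaker headline claim.
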